# Comparison of 22G standard and Franseen needles in endoscopic ultrasound-guided fine-needle aspiration for diagnosing pancreatic mass lesions: Study protocol for a controlled trial

**DOI:** 10.1186/s13063-019-3946-7

**Published:** 2019-12-30

**Keywords:** EUS-FNA, Puncture needle, Franseen needle, Pancreatic mass, Malignancy, Diagnostic yield

## Abstract

**Background:**

Endoscopic ultrasound-guided fine-needle aspiration (EUS-FNA) was developed with the aim of further improving the diagnostic performance of endoscopic ultrasound. Although novel puncture needles have been specifically designed for collecting sufficient tissue specimens, clinical studies have indicated no clear difference in diagnostic performance between these novel needles and conventional puncture needles. Recently, a needle with Franseen geometry was developed specifically for EUS-FNA biopsy. Due to the characteristic shape of its tip, the Franseen needle is expected to be effective for scraping tissues, thus potentially increasing the diagnostic accuracy of EUS-FNA biopsy. We plan to carry out a prospective, multicenter, open-labeled, controlled trial to compare conventional and Franseen needles in terms of the diagnostic accuracy of EUS-FNA for evaluating the malignancy of pancreatic mass lesions.

**Methods/design:**

The study will enroll 520 patients with pancreatic mass managed at any of 21 participating endoscopic centers. Lesion samples obtained using 22G conventional and Franseen needles will be assessed to compare the efficacy and safety of these two types of needles in EUS-FNA for evaluating the malignancy of mass lesions in the pancreas. Tissue samples will be fixed in formalin and processed for histologic evaluation. For the purpose of this study, only samples obtained with the first needle pass will be used for comparing the: (i) accuracy of the malignancy diagnosis, (ii) sensitivity and specificity for the malignancy diagnosis, (iii) procedure completion rate, (iv) sample cellularity, and (v) incidence of complications. Patient enrollment begins on July 17, 2018.

**Discussion:**

The outcomes of this study may provide insight into the optimal needle choice for evaluating the malignancy of pancreatic solid lesions, thus aiding in the development of practice guidelines for pancreatic diseases.

**Trial registration:**

University Hospital Medical Information Network Clinical Trials Registry (UMIN-CTR), UMIN000030634. Registered on 29 December 2017.

http://www.umin.ac.jp/

Version number: 01.2017.12.28.

## Background

Endoscopic ultrasound (EUS) is recognized as an effective tool for detecting, diagnosing, and T-staging small lesions in the vicinity of the gastrointestinal tract [1]. However, EUS has limited use in distinguishing between benign and malignant lesions. EUS-guided fine-needle aspiration (EUS-FNA) was developed with the aim of further improving the diagnostic performance of EUS. The use of EUS-FNA has become widespread because this technique provides a great deal of information that can be used to determine which treatment strategy is best suited in each case, depending on the disease stage and other properties. EUS-FNA is currently used especially for the diagnosis of pancreatic tumors. To date, clinical data have shown that EUS-FNA contributes to the treatment results in patients with pancreatic cancer [2]. In patients with solid pancreatic masses, EUS-FNA has a diagnostic sensitivity of 54–96%, specificity of 96–98%, and accuracy of 83–95% [3–6]. Cytopathology plays an important role in improving the diagnostic yield. While cytology can differentiate between benign and malignant lesions, histology evaluation must be performed in order to establish the lesion subtype and pathogenesis. It is thus necessary to collect sufficient tissue specimens to facilitate accurate histological evaluation. In this context, it is important to use puncture needles suitable for the particular features and location of the evaluated lesion [7].

Puncture needles specifically designed to collect sufficient tissue specimens have been developed, but clinical studies have not reported any clear differences in diagnostic performance for different needles [8–10]. Recently, a needle with Franseen geometry (Acquire™; Boston Scientific Corporation, Natick, MA, USA) was designed for EUS-FNA biopsy. Due to the characteristic shape of its tip, the Franseen needle is expected to be effective for scraping tissues, allowing collection of larger specimens, and thus potentially facilitating the diagnosis of lesions that are typically difficult to diagnose based on cytology alone, such as autoimmune pancreatitis and pancreatic endocrine tumors [11]. Therefore, the impact of the needle type (conventional or Franseen) on the diagnostic yield warrants further study. We plan to carry out a controlled trial to compare the diagnostic yield of 22G conventional needles (Expect™; Boston Scientific Corporation, Natick, MA, USA) and of the newly developed Franseen needles (Acquire™) used for EUS-FNA sampling of pancreatic mass lesions.

## Methods/design

### Ethics approval and patient consent

The study was approved by the Wakayama Medical University Ethics Committee (Institutional Review Board number 2135). Informed consent will be obtained from all patients. The trial was registered with the University Hospital Medical Information Network (trial registration number UMIN000030634). This protocol was prepared in conformance with the Standard Protocol Items: Recommendations for Interventional Trials (SPIRIT) guidelines (Additional file 1).

### Study aims and design

The major objective of this study is to determine whether the Franseen needle is superior to the conventional needle for accurate diagnosis of malignancy in patients with pancreatic mass. This multicenter controlled study will compare 22G conventional and Franseen needles in terms of the efficacy and safety of EUS-FNA for evaluating the malignancy of mass lesions in the pancreas. As this comparative study mainly aims to assess the specimens obtained with the first puncture, no special protocol will be established regarding the technique for the second or subsequent punctures. Outcomes of the second and subsequent EUS-FNA procedures will be used to make the final diagnosis of the pancreatic mass for patients with non-resection. The flowchart in Fig. 1 illustrates the recruitment, allocation, and follow-up process.

**Fig. 1 Fig1:**
[figure not shown]
Flowchart illustrating the recruitment, allocation, and follow-up process

### Outcomes

The primary endpoint in this study will be diagnostic accuracy for malignancy, whereas secondary endpoints will include (i) sensitivity and specificity for diagnosis of malignancy, (ii) procedure completion rate, (iii) sample cellularity, and (iv) incidence of complications.

### Analysis target group

In the effectiveness analysis population, the full analysis set (FAS) is the main analysis and the per-protocol set (PPS) analysis is performed as a reference. In the safety analysis target population, all test samples are analyzed.

The FAS is defined as all registered cases excluding those who do not meet the eligibility criteria of this study after registration. The safety analysis target population is defined as cases who received part or all of the protocol treatments among all registered cases. The PPS is defined as cases excluding those meeting the following criteria from the FAS:
Inability to evaluate efficacy due to inadequate observationCritical deviation violating the specifications of the protocol

### Major analysis and judgment criteria

The primary objective of this study is to determine whether the test diagnostic device (22G Acquire™ needle) is superior to the conventional diagnostic device (22G Expect™ needle) for accurate diagnosis of malignancy. If the rate of correct diagnosis is significantly higher in the Franseen needle group than in the conventional needle group, it will be concluded that the test diagnostic device (22G Acquire™ needle) is a more promising diagnostic device. If the difference is not significant, it will be concluded that the Franseen needle is not a superior diagnostic device compared with the conventional needle. The main analysis will use the Mantel-Haenszel test because adjustment factors other than the site are used for stratification in the FAS. When comparing the two groups in terms of the rate of correct diagnosis, the difference will be considered significant if the *p* value in the Mantel-Haenszel test is below the significance level taken into consideration in the power analysis (a two-sided significance level of α = 0.05). The Clopper-Pearson exact test will be used to estimate the 95% confidence interval of accuracy for the diagnosis of malignancy in each group. In addition, logistic regression analysis with adjustment for covariates (other than site) will be used to calculate the odds ratio (with 95% Wald confidence interval) for the outcome associated with using the Franseen needle versus using the conventional needle.

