### Sample size calculation

There have been no reports on the rate of correct diagnosis of pancreatic masses evaluated by EUS-FNA using the 22G Franseen needle. However, a previous study focusing on puncture needles designed to sample sufficient tissue for core biopsy reported that the rate of correct diagnosis was 75% for the conventional needle (EchoTip Ultra needle) compared to 80% for the specially designed EchoTip ProCore needle [10]. Assuming that the rate of correct diagnosis is higher when using the Franseen needle than when using the EchoTip ProCore needle, we expect the rate of correct diagnosis of pancreatic mass malignancy to be 85% when EUS-FNA is performed using the Franseen needle. A sample size of 500 participants (250 per group) would provide a power of 80% (1 − β) considering a two-sided significance level of α = 0.05 (chi-square test) for between-group comparisons of diagnostic rate. Assuming that approximately ten participants per group will have to be considered ineligible for inclusion in the final analysis, the target sample size in this study is established at 520 participants (260 per group).

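### A non-significant primary test is pre-specified to mean that the Franseen needle is not superior, which a superiority trial with 80% power and no margin cannot show

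*Protocol article*

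**What the plan says.** The trial has a superiority aim (Study aims and design): "The major objective of this study is to determine whether the Franseen needle is superior to the conventional needle". No equivalence or non-inferiority margin and no smallest relevant difference appears anywhere in the article.

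The section Major analysis and judgment criteria names the test, "The main analysis will use the Mantel-Haenszel test", at a two-sided 5% level in the full analysis set. It then allows two outcomes:

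- If the Franseen rate is significantly higher, "it will be concluded that the test diagnostic device (22G Acquire™ needle) is a more promising diagnostic device".
- Otherwise, "If the difference is not significant, it will be concluded that the Franseen needle is not a superior diagnostic device".

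The same section plans two kinds of interval. Clopper-Pearson intervals will "estimate the 95% confidence interval of accuracy for the diagnosis of malignancy in each group". A covariate-adjusted logistic model will give an odds ratio for Franseen versus conventional with a 95% Wald interval. Neither enters the decision rule.

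Under Sample size calculation, "A sample size of 500 participants (250 per group) would provide a power of 80"%, for an expected 85% with the Franseen needle against 75% with the conventional one, "considering a two-sided significance level of α = 0.05 (chi-square test").

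**The concern.** The second branch of the rule is a statement about the device, and it follows from the p value alone. Failure to reject the null hypothesis can mean that there is no advantage, that there is a modest one, or that the assumed advantage is real and this trial missed it. The rule has no outcome for superiority simply not having been shown.

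The article says that the results may help to develop practice guidelines, and its Background section notes that earlier studies of specially designed needles found no clear differences. If the rule were applied literally, an inconclusive trial would be reported as a negative finding about the needle and could be taken to confirm that picture.

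**Working it through.** **Inputs (Sample size calculation):** 250 evaluable patients per group, control accuracy p1 = 0.75, Franseen accuracy p2 = 0.85, two-sided α = 0.05, chi-square test. The same section cites an earlier study of other needles: "the rate of correct diagnosis was 75% for the conventional needle (EchoTip Ultra needle) compared to 80"% for a specially designed needle. That 80% serves below as an illustrative smaller effect.

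**Step 1: reproduce the plan's figure.** With p̄ = (p1 + p2)/2, pooled variance and no continuity correction:

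n per group = [1.960·√(2p̄(1−p̄)) + 0.8416·√(p1(1−p1) + p2(1−p2))]² / (p2−p1)²

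= [1.960·√0.32 + 0.8416·√0.315]² / 0.01 = 249.98, so 250. The plan's figure reproduces exactly. Enumerating the binomial distributions for the same test gives 80.3% power.

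**Step 2: how often the rule returns the negative verdict.**

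Power = Φ{[(p2−p1)·√n − 1.960·√(2p̄(1−p̄))] / √(p1(1−p1) + p2(1−p2))}, with n = 250

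- True 85% vs 75%: (1.581 − 1.109)/0.561 = 0.842; power 80.0%; negative verdict 20%.
- True 80% vs 75%: (0.791 − 1.157)/0.589 = −0.622; power 26.7%; negative verdict about 73%.

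By the same formula the negative verdict has probability 41% at a true 83%, 52% at 82% and 88% at 78%. A continuity-corrected test would have 77.2% power at 85% and 23.4% at 80%, so the negative verdict would be slightly more frequent (22.8% and 76.6%).

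**Step 3: a concrete non-significant result.** Take 205/250 (82.0%) against 188/250 (75.2%), a difference of 6.8 points.

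- Test: z = 1.85, not significant. The rule returns the negative verdict.
- Difference: 0.068 ± 1.96·√[(0.82·0.18 + 0.752·0.248)/250] = 0.068 ± 1.96·0.0366, or −0.4 to +14.0 points.
- Unadjusted odds ratio: (205·62)/(188·45) = 1.50. The standard error of its logarithm is √(1/205 + 1/45 + 1/188 + 1/62) = 0.220, which gives 0.98 to 2.31.
- Design effect on the odds ratio scale: (0.85/0.15)/(0.75/0.25) = 1.89.

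Both intervals include no effect, and both include the full effect assumed at the design stage. Such a result is inconclusive. From 188/250, the first count to reach significance is 206/250, a difference of 7.2 points.

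**The case against.** **The wording may be shorthand.** Read with the stated objective, the sentence could mean only that the superiority criterion was not met. The text claims neither equivalence nor absence of any benefit. That reading is possible, but the sentence is phrased as a conclusion about the device, it sits under judgment criteria, and nothing elsewhere qualifies it.

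**The percentages are ordinary type II error.** This is correct. The 20% follows directly from the disclosed 80% power, and the 73% rests on a gain seen with a different needle, which the authors expect the Franseen needle to exceed. Rewording changes neither probability. They matter because the rule turns each such miss into a negative conclusion.

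**A between-group interval is already planned.** A reader might infer that the plan leaves no means of telling an inconclusive result from one that shows no useful gain. The documents do not support that: the odds ratio has a 95% Wald interval, and in the worked example its unadjusted counterpart makes the inconclusiveness visible. What stands is narrower. The rule does not use that interval, and none is planned on the risk-difference scale. The latter is partly a choice of scale, and a separate analysis plan might add it.

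**The 10-point design difference might seem a natural threshold for declaring no relevant benefit.** The document gives it as the expected effect and nowhere as the smallest relevant one. With 193/250 against 188/250 the interval is 0.020 ± 1.96·0.0381, or −5.5 to +9.5 points. A 10-point threshold would allow a claim of no relevant benefit while gains of 5 to 9 points remain compatible with the data.

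**Conclusion.** The concern holds as a defect of interpretation. The pre-specified conclusion after a non-significant test goes further than the design can support: with 250 per group and 75% control accuracy it would be drawn in 20% of trials at a true 85% and in about 73% at a true 80%. These figures use the unstratified chi-square test of the sample size section; the planned Mantel-Haenszel test may differ slightly. The 80% is illustrative.

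A reader might infer that the primary analysis itself is unsound. It is not: the sample size reproduces, and the test, its type I error and the planned estimates are unaffected. The severity is therefore moderate. The sentence should still be corrected, because it decides what the trial may claim after a null result.

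**What to change.** Replace the sentence with: *If the difference is not significant, superiority has not been demonstrated, and the result will be interpreted from the between-group effect estimate with its 95% confidence interval.*

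Use the planned odds ratio for this. Preferably add a Mantel-Haenszel risk difference with a 95% interval, so that the estimate is also available on the scale used to size the trial. Do not attach a 10-point threshold for no relevant benefit, since the document does not define 10 points as the smallest relevant difference.

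The cost is one reworded sentence and one more line of output. The negative statement becomes less definite. No patients are added and the primary test does not change.

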### Secondary efficacy analysis

#### Sensitivity and specificity for the diagnosis of malignancy

Sensitivity analysis is restricted to the subjects with malignancy and specificity analysis is restricted to the subjects without malignancy.

Sensitivity and specificity (with the Clopper-Pearson exact 95% confidence interval) will be estimated for each group in the FAS. The chi-square test will also be conducted, and the odds ratio (with 95% confidence interval) will be calculated to evaluate the between-group differences in sensitivity and specificity. The adjusted odds ratio (with 95% confidence interval) will be calculated using logistic regression analysis including the assignment factors.

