### Treatment allocation and blinding

Each subject will be assigned to either of the treatment methods at a ratio of 1:1 according to a web-based registration program system (based on dynamic allocation by the minimization method). Dynamic allocation by the minimization method is designed to minimize imbalance between treatments taking stratification factors into account. For assignment to prevent large bias. Based on the baseline factors for treatment allocation, including the diameter of tumor, site where the tumor is located, pattern of contrast computed tomography, and institution, an imbalance score is computed. The treatment with the lowest imbalance score is assigned.

The registration secretary will strictly control the program to prevent leaking of the assignment information. Blinding will not be used in this study.

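### The specificity comparison is too sparse for the chi-square test and the 21-institution logistic model; for completion and complications the same model conflicts with the primary analysis and is overparameterised if events are few

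*Protocol article*

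**What the plan says.** All references are to the protocol article.

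- *Sensitivity and specificity for the diagnosis of malignancy*: specificity is analysed only in subjects without malignancy. Each arm gets a Clopper-Pearson interval. The arms are compared by a chi-square test and an odds ratio, and then: "The adjusted odds ratio (with 95% confidence interval) will be calculated using logistic regression analysis including the assignment factors". *Procedure completion rate* and *Incidence of complications* prescribe the same set of methods.
- *Treatment allocation and blinding*: the minimisation factors are tumour diameter, "site where the tumor is located, pattern of contrast computed tomography, and institution". *Setting* gives 21 centres.
- *Major analysis and judgment criteria*: the primary Mantel-Haenszel test leaves site out of the stratification, and the primary model is "logistic regression analysis with adjustment for covariates (other than site").
- *Background*: for solid pancreatic masses the literature is summarised as "diagnostic sensitivity of 54–96%, specificity of 96–98%, and accuracy of 83–95" per cent.

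The article states no expected share of benign masses, no complication rate and no completion rate. For these comparisons between arms it names no exact, penalised or other sparse-data method.

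**The concern.** Read plainly, the adjusted secondary models contain needle, three tumour factors and 20 institution terms. The primary model, with far more events, leaves site out. For specificity, the events are false positives in what is probably a small benign subgroup. Ordinary maximum likelihood has no finite solution when some combination of covariates separates events from non-events, and with a handful of events over 21 centres that is to be expected. The software would then print a very large or missing odds ratio with a meaningless Wald interval. The unadjusted odds ratio is likewise zero or undefined whenever an arm has no false positive. A substitute method would have to be chosen after the data are seen, in a trial where only the pathologists are blinded to the needle. Specificity is a named secondary endpoint, so its method should work on the data the article leads one to expect.

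**Working it through.** **The plan's own figure.** Inputs from *Sample size calculation*: "the rate of correct diagnosis was 75% for the conventional needle (EchoTip Ultra needle"), "we expect the rate of correct diagnosis of pancreatic mass malignancy to be 85" per cent, and "considering a two-sided significance level of α = 0.05 (chi-square test"). The two-proportion formula with pooled variance and no continuity correction gives 250 per group and power 0.800. This matches "A sample size of 500 participants (250 per group) would provide a power of 80" per cent. The expected number of incorrect diagnoses for the primary endpoint is 250 × 0.25 + 250 × 0.15 = 100.

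**Model size.** Needle (1) + three tumour factors, each taken as binary (3) + institutions (21 − 1 = 20) = about 24 parameters. For the primary endpoint even this model would have 100/24 ≈ 4.2 events per parameter; without institution it has 100/4 = 25.

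**Specificity: expected counts.** False positives = 500 × benign share × (1 − specificity). The benign share is assumed to be 5–30%; specificity is 96–98% from *Background*. Under 1:1 allocation each arm gets half.

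| Benign patients (assumed) | False positives, total | Per arm |
|---|---|---|
| 25 (5%) | 0.5–1 | 0.25–0.5 |
| 50 (10%) | 1–2 | 0.5–1 |
| 100 (20%) | 2–4 | 1–2 |
| 150 (30%) | 3–6 | 1.5–3 |

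An expected 5 per arm (10 in total) would need 10/0.04 = 250 to 10/0.02 = 500 benign patients.

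The chance that at least one arm has no false positive is 1 − (1 − s^m)², with s the specificity and m the benign patients per arm. For 100 benign patients at 96%: 1 − (1 − 0.96^50)² = 0.24. For 50 at 98%: 1 − (1 − 0.98^25)² = 0.84.

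**Specificity: chi-square test.** Exact binomial enumeration of the type I error at nominal 0.05:

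- 12 per arm, 3% false positives: 0.0005
- 25 per arm, 3–4%: 0.006–0.012
- 50 per arm, 2–4%: 0.013–0.039
- 75 per arm, 2–4%: 0.029–0.047

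The test is conservative throughout, not inflated.

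**Specificity: adjusted model.** Simulation used a 3% false-positive rate, three binary covariates, patients spread at random over 21 institutions, and 200 runs per setting (simulation error at most √(0.5 × 0.5/200) ≈ 3.5 percentage points). Share of runs in which the needle odds ratio has no finite estimate:

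| Benign patients | With institution | Without institution |
|---|---|---|
| 25 | 100% | 92% |
| 50 | 97% | 74% |
| 100 | 72% | 40% |
| 150 | 37% | 19% |

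With institution in the model, some coefficient diverged in every run. Dropping institution helps but is not enough.

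**Complications (rate assumed; FAS about 500).**

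| Rate | Events | Expected per arm | Events per parameter (÷ 24) | Chi-square type I error | Needle odds ratio not finite |
|---|---|---|---|---|---|
| 0.5% | 2.5 | 1.25 | 0.1 | 0.022 | 46% |
| 1% | 5 | 2.5 | 0.2 | 0.046 | 14% |
| 2% | 10 | 5 | 0.4 | 0.046 | 0.5% |
| 3% | 15 | 7.5 | 0.6 | 0.051 | 0% |

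The last column is from the model with institution. Some institution coefficients diverged in all runs at rates up to 5%, but from 2% upward the needle coefficient almost always remained estimable. At 1%, about 14% of runs still had no finite needle odds ratio after institution was dropped. The cause is an empty arm, whose probability is 1 − (1 − 0.99^250)² ≈ 0.16.

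For completion the article gives nothing to compute from.

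**The case against.** A reader might infer that the chi-square test is invalid, and the adjusted odds ratio inestimable, for specificity, completion and complications alike. The documents do not support that. They give no complication or completion rate, so rarity there is an assumption. At an assumed 1–3% of complications the chi-square test is close to its nominal level, and from 2% upward the needle odds ratio is almost always finite. Nor is *invalid* the right word for specificity: the sparse chi-square test errs on the conservative side. Fisher's test will not restore the missing power.

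Three further objections have weight.

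- The 96–98% describes EUS-FNA in the literature, not a single first pass read by histology alone. If non-diagnostic samples from benign masses count as incorrect, specificity would be lower and events more numerous. The article does not say how they count.
- The article does not say that institution enters as 20 fixed indicators; the coding may be settled in an analysis plan that is not shown. *Site* in the primary analysis might even mean tumour site. In either reading, though, the primary model leaves out a factor that the secondary wording keeps, so the sections still need reconciling.
- The Clopper-Pearson intervals for each arm stay valid with zero events, so the endpoints would not be left without any result.

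These points limit the claim. They do not remove the specificity problem at the only specificity figure the article gives.

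**Conclusion.** The concern holds for specificity. With 25–150 benign patients assumed and specificity of 96–98%, expected false positives are 0.25–3 per arm. The chi-square test is conservative and low in power, and the adjusted needle odds ratio often has no finite value: 37–100% of simulated runs with institution, 19–92% without, at a 3% false-positive rate. This rests on the assumed benign share and on not counting non-diagnostic benign samples as incorrect.

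For complications and completion, only two statements are supported. The model with institution is overparameterised if events are few (about 0.2–0.6 per parameter at an assumed 1–3%), and it is inconsistent with the primary model's exclusion of site. The chi-square test is acceptable there unless the event rate is well below about 2%.

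The superiority conclusion depends on the primary test alone, so it and the sample size stand.

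**What to change.** - **Specificity.** Compare arms with a mid-p or Fisher exact test (mid-p is the less conservative). Report the risk difference with an exact or Newcombe interval, which remains defined when an arm has no false positive. Take any adjusted odds ratio from Firth-penalised logistic regression on needle plus the tumour factors, without institution fixed effects.
- **Completion and complications.** Drop institution as a fixed effect, in line with the primary model. Keep the chi-square test, with a pre-stated switch to the exact or penalised method when events are sparse, for example when an expected cell count is below 5.
- **Wording.** State whether *site* in the primary analysis means institution or tumour site, and list the covariates of each secondary model. State also how a non-diagnostic first-pass sample from a benign mass counts towards specificity.

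The cost is a few sentences and standard software options. The downside is slight conservatism of exact tests. No additional patients or data are needed.
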